#### Process evaluation

The process evaluation will be undertaken ‘to explain discrepancies between expected and observed outcomes, to understand how context influences outcomes, and to provide insights to aid implementation’. Interviews will be held with a subgroup of participants (*n*=6), healthcare professionals (*n*=3) and clinical triallists (*n*=2). These interviews will focus only on the experience of participating in the clinical trial, rather than questions about the intervention itself. The purpose of the process evaluation is to inform future roll-out of the intervention if proven to be clinically and cost-effective.

The study may be monitored, or audited in accordance with the current approved protocol, GCP, relevant regulations and standard operating procedures. All researchers involved in the study will have up to date GCP training. Adherence to intervention protocols will be reviewed periodically. The independent Trial Steering Group, consisting of clinical and psychosocial experts, PPI, statistician and trials manager will meet every six months to review trial conduct throughout the duration of the trial period.

##### Health economic analysis

Cost-effectiveness analyses to calculate quality-adjusted life years (QALYs) will be estimated from the EQ-5D-5L questionnaire and mortality data, using the area-under-the-curve method. A QALY is a measure of the state of health of a person, adjusted to reflect quality of life. One QALY equates to one year lived in perfect health [19]. Similarly, costs will be estimated at the patient level. Mean between-group differences in QALYs and costs will be estimated using a regression-based approach, including adjustment for baseline covariates and interaction terms for pre-defined sub-groups, and allowing for clustering at hospital and/or practitioner level. Results will be presented as an Incremental Cost-Effectiveness Ratio (ICER) if appropriate. Non-parametric bootstrapping will be used to estimate confidence intervals around estimated cost differences and ICERs.

A simple modelling approach will also be used to estimate the costs and health impacts of surgical complications over a lifetime horizon. This long extrapolation is necessary to reflect any mortality or lasting quality of life decrement associated with surgical complications. There will be no attempt to estimate the long-term impact of improved diabetes management related to the intervention, as it will be difficult to predict the duration over which any improvements will be maintained. This is likely to be a conservative assumption that will under-estimate the QALY gain and cost-effectiveness of intervention if it proves to be effective. Model parameters will be estimated from the trial and from other published sources.

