## Trial design

Spotlight is an exploratory multicentre, parallel group, individually randomised RCT. Sites are primary and secondary care NHS centres located in Southampton, Wessex, Portsmouth, Bradford, Blackburn and South-West London. It will compare consultation length, biomedical and psychosocial outcomes in adults with type 1, type 2 or pre-diabetes attending routine outpatient appointments for their diabetes care. The number needed for a two-sample *t* test with standardised effect size of 0.50 at alpha=0.05, 90% power is 86 per group [9]. Thus, we will recruit a minimum of 100 participants for the control group and 100 participants for the intervention groups to allow for potential dropout. Previous feasibility data from real-world evidence collection has demonstrated feasibility, acceptability and improved consultations across three centres in the UK and USA [10].

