### Randomisation

Once the consent process has been completed, study participants will be randomised into either the intervention group or control group for 12 months. We will randomise on a 1:1 basis using computerised randomisation software. Sealed envelope online software randomisation will be used. Randomisation is blocked and stratified by centre (using random permuted blocks) to ensure groups are balanced.

Those randomised to the intervention group will be asked to complete study questionnaires every three months and the Spotlight Consultation pre-clinic assessment at baseline and follow-up scheduled routine outpatient appointments (Table 1). The results of the Spotlight Consultation digital health assessment will be discussed between the participant and healthcare professional during the outpatient visit along with identified matched care pathways and agreement made on best-fit action plan.

**Table 1 Tab1:** Psychosocial questionnaires

Construct	Measure	Relibaility
Diabetes Distress	DDS [11]	*α*’s=.94
Depression	PHQ-2 [12]	*α*’s=.86
Anxiety	GAD-7 [13]	*r* = 0.782
Engagement	Self-Care Inventory (SCI) [14]	*R*=0.89
Treatment Satisfaction/Utility	Diabetes Treatment Satisfaction Questionnaire [15]	*a* = 0.92
Health Resource Utility	EQ5D [16]	*α*’s=.89
Well-being	WHO-5 [17]	*α*’s=.90
HCP Burnout	Maslach Burnout Inventory [18]	*α*’s=.90

All measures will be administered at baseline, 3, 6, 9 and 12 months

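### The planned bootstrap confidence interval around the ICER cannot be interpreted if replicates include QALY differences at or below zero, which may well happen with 100 per arm if the 12-month gain is small

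*Protocol article*

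**What the plan says.** Under Health economic analysis, the protocol article says that QALYs "will be estimated from the EQ-5D-5L questionnaire and mortality data, using the area-under-the-curve method". It continues: "Mean between-group differences in QALYs and costs will be estimated using a regression-based approach", with adjustment for baseline covariates and allowance for clustering. It then says "Results will be presented as an Incremental Cost-Effectiveness Ratio (ICER) if appropriate", followed directly by "Non-parametric bootstrapping will be used to estimate confidence intervals around estimated cost differences and ICERs".

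The interval on the ICER is the only summary of the joint uncertainty in costs and QALYs that the article names. It gives no criterion for when an ICER is appropriate, no rule for replicates with a zero or negative QALY difference, and neither a QALY SD nor an expected QALY gain.

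The number of participants was set for consultation duration: under Trial design, a "standardised effect size of 0.50 at alpha=0.05, 90% power is 86 per group", raised to 100 per arm "to allow for potential dropout".

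**The concern.** A confidence interval needs values that can be put in order from worse to better. The ratio of the cost difference to the QALY difference loses that order when the QALY difference changes sign. A negative ratio can mean cheaper and better or dearer and worse. A positive ratio can mean paying more for a gain or saving money at the price of a loss. Near a zero QALY difference the ratio also jumps between very large positive and very large negative values. Limits taken from such a set of replicates do not tell a reader whether the intervention is good value.

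Cost-effectiveness is part of the stated aim under Objective. The abstract's Discussion and the Process evaluation section both link later use of the tool to its being shown cost-effective. If the reported interval cannot be read, the summary of uncertainty will have to be chosen after the data are seen.

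**Working it through.** **The plan's own figure.** For a standardised effect of 0.50, two-sided alpha 0.05 and 90% power, the normal approximation gives 2 × (1.960 + 1.282)² / 0.50² = 84.1, so 85 per group. The exact t-test solution is 85.03, so 86. The stated 86 is reproduced. It concerns consultation duration, not QALYs.

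**Inputs.**
- n = 100 per arm ("we will recruit a minimum of 100 participants for the control group and 100 participants for the intervention groups"), allocated 1:1 (Randomisation section).
- QALYs over 12 months, with measures at 0, 3, 6, 9 and 12 months (Table 1).
- QALY SD: not in the article; assumed 0.10 to 0.25.
- True QALY gain d: not in the article; shown for 0.01, 0.02, 0.05 and 0.10.
- Baseline adjustment and clustering are ignored.

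**Why the order is lost.** Four replicates:
- +200 / +0.01 = 20,000 (dearer, better)
- −200 / −0.01 = 20,000 (cheaper, worse)
- −200 / +0.01 = −20,000 (dominant)
- +200 / −0.01 = −20,000 (dominated)

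Each pair has one ratio and two opposite meanings.

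**How often it would arise.** SE = SD × √(2/n). The chance that the estimated difference is at or below zero is Φ(−d/SE). The chance that more than 2.5% of replicates are at or below zero is Φ(1.96 − d/SE). The 2.5% mark is where the lower 95% limit for the QALY difference itself reaches zero.

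Worked example, SD 0.15 and d = 0.02: SE = 0.15 × √0.02 = 0.0212 and d/SE = 0.943. Then Φ(−0.943) = 17.3% and Φ(1.017) = 84.5%.

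Chance that more than 2.5% of replicates are at or below zero, 100 per arm:

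| SD | SE | d = 0.01 | d = 0.02 | d = 0.05 | d = 0.10 |
|---|---|---|---|---|---|
| 0.10 | 0.0141 | 89.5% | 70.7% | 5.8% | 0.0% |
| 0.15 | 0.0212 | 93.2% | 84.5% | 34.6% | 0.3% |
| 0.20 | 0.0283 | 94.6% | 89.5% | 57.6% | 5.8% |
| 0.25 | 0.0354 | 95.3% | 91.8% | 70.7% | 19.3% |

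In SD units, so without assuming an SD, the chance is 97.5% for no effect, 89% for 0.1 SD, 71% for 0.2 SD, 44% for 0.3 SD and 6% for 0.5 SD. With 86 per arm these become 97.5%, 90%, 74%, 50% and 9%.

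**Does a positive point estimate protect?** In the worked example, the chance of a positive estimate together with more than 2.5% of replicates at or below zero is 84.5% − 17.3% = 67.2%.

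**Coverage.** A simulation assumed a QALY SD of 0.20, a cost SD of 1,500, cost differences of ±100 and gains of 0.01 to 0.10, with 2,000 trials per setting and 1,000 replicates each, drawn from normal distributions. Nominal 95% percentile intervals covered the true ratio about 96–99% of the time. The failure is therefore one of interpretation and not of numerical under-coverage.

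**The case against.** **The ICER is conditional.** An interval around the ICER exists only if an ICER is presented, and a QALY difference near zero is an obvious reason not to present one. This has some force, but the article gives no criterion. If the judgement rests on the point estimate, it misses the common case above, in which a positive estimate goes with replicates on both sides of zero.

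**The type of bootstrap interval is not stated, and an analysis plan may say more.** Both are true: the article does not specify percentiles, and nothing in it excludes net monetary benefit. But the point does not rest on an omission. The article commits to an interval on the ICER, and the loss of order belongs to the ratio itself, however its replicates are turned into limits.

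**The likelihood rests on assumed inputs.** This stands. For a gain of 0.10 the problem is uncommon. Baseline adjustment would also help. With an assumed baseline correlation of 0.6, the worked example's SE falls to 0.0212 × √(1 − 0.36) = 0.017, and the chance falls from 84.5% to Φ(1.96 − 0.02/0.017), about 78%. Clustering could push the other way.

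**The consequence is limited.** This also stands. Trial design calls the trial exploratory, and cost-effectiveness is listed last among the secondary outcomes. A reader might infer that cost-effectiveness uncertainty would be misreported or that the whole economic analysis is invalid. The documents do not support that: simulated coverage was at or above nominal, and the regression estimates and the cost-difference interval are unaffected.

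**Conclusion.** The point holds as a defect in a stated method. An interval on the ICER is not interpretable when replicates include QALY differences at or below zero. Under an assumed SD of 0.10 to 0.25 with 100 per arm, that condition is more likely than not for true gains of 0.01 to 0.02, uncertain at 0.05 and uncommon at 0.10. A small gain is plausible because the Control arm section says the diabetes treatment itself does not change in either arm, and the economic section declines to extrapolate longer-term benefit. The article does not establish it, however, so an unconditional claim that the interval will fail would go too far. Where replicates stay clear of zero, the interval can be read. The matter is worth correcting before analysis, and it affects neither the primary outcome nor the sample size.

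**What to change.** In the health economic text, replace the confidence interval around the ICER with incremental net monetary benefit, λ × (QALY difference) − (cost difference), and its 95% interval at willingness-to-pay thresholds λ stated in advance. Take it from the same bootstrap, resampling each participant's costs and QALYs together. The measure is linear, so it keeps the order that the ratio loses. In the four-replicate example, the dominant result gives 0.01λ + 200 and the dominated one −0.01λ − 200. The two trade-offs give 0.01λ − 200 and 200 − 0.01λ, again opposite in sign.

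Add the cost-effectiveness plane and the acceptability curve. Report the ICER as a point estimate only, and keep the interval for the cost difference as planned.

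The cost is a few sentences of analysis wording. No new data or replicates are needed. The small downside is that the thresholds must be fixed beforehand.

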## Data management plan

A data management plan (DMP) providing full details of the study-specific data management strategy for the trial will be available and a trial schedule with planned and actual milestones, CRF tracking and central monitoring for active trial management created. Data queries will either be automatically generated within the eCRF, or manually raised by the study team, if required. All alterations made to the eCRF will be visible via an audit trail which provides the identity of the person who made the change, plus the date and time.

At the end of the study after all queries have been resolved and the database frozen, the PI will confirm the data integrity by electronically signing all the eCRFs. The eCRFs will be archived according to Southern Health policy and a PDF copy including all clinical and Meta data returned to the PI for each participant. All data will be collected and stored in a secure password protected computers. Access to systems is severely restricted to specific research staff. Data collected during the course of the research will be kept strictly confidential and only accessed by authorised members of the trial team. All participants will be allocated an individual trial identification number and anonymised transcripts will be stored on a secure database. Audio recordings will be destroyed immediately following quality assessment of transcription.

Only clinical trials staff will have access to the final trial dataset for data cleaning and analyses.

## Potential risks

The risks associated in taking part are very small. Taking part may make participants think more about their own mood and how they feel about their diabetes, their approach to self-management and views on diabetes burden and its impact more broadly. The study team will make every effort to avoid compromising a participant’s confidentially that may result in serious negative social, legal or economic ramifications for the participant. The team will adhere to ethics regulations during this study.

### Adverse event reporting

Any and all untoward medical occurrence in a participant or clinical study participant, diabetes-related or otherwise, which does not necessarily have a causal relationship with study treatment or participation. An AE can therefore be any unfavourable and unintended sign (including an abnormal laboratory finding), symptom or disease temporally associated with the study treatment or participation (regardless of causality assessments). Serious adverse events are not anticipated due to the nature of the study.

Formal stopping rules do not apply as there are no anticipated problems that are detrimental to the participant.

## Data monitoring committee

A external data monitoring committee will be established to provide external independent oversight of the conduct of the clinical trial. This committee will meet every 6 months and consist of individuals from lay and multi-disciplinary teams.

## Strengths and limitations of the study

*Novelty of the intervention / the fact that it addresses an important gap*

*Choice of outcome measures will enable a complete evaluation of both clinical outcomes and cost-effectiveness*

*Sample size and number of sites will make the results representative of a wide population and centres with differences in practice*

*Intervention can be delivered face-to-face or remotely due to COVID and practical issues*

*COVID-19 may create delays and recruitment problems*

*Intervention requires use of tablet device (provided) however is unsuitable for adults with low literacy or poor English*

## Dissemination plan

Results of the study will be submitted for publication in peer reviewed journals and for presentation at national and international scientific conferences (American Diabetes Association, Advanced Therapeutics and Technologies in Diabetes, Diabetes UK Annual Professional Conference). Results will also be disseminated to trial participants via letter and more broadly via patient conferences and advocacy group meetings.

## Trial status

Protocol v.1.10; 24 March 2021

Recruitment start: 18 October 2021; recruitment completion: 31 March 2022

## Data Availability

On request from the PI.
